## Abstract

**Background::**

According to the national census, China has gradually become an aging society; moreover, aging has become an irreversible worldwide trend in the twenty-first century. Aging can lead to decreased physical function, mobility, cardiopulmonary function and quality of life (QOL). The feasibility and benefits of core strength training (CST) and Tai Chi Chuan (TCC) in older adults (including improving cardiovascular, musculoskeletal, and mental health outcomes) have been confirmed in previous studies. To date, these exercise programmes have not been systematically compared, and the potential benefits of their combined use have not been tested. The primary objective of this **s**tudy protocol is to evaluate the effects of CST compared to those of TCC on the function of the musculoskeletal system and the cardiopulmonary system in older adults.

The second objective is to test the effectiveness of combined physical training that incorporates CST and TCC.

**Methods::**

A randomized, single-blind, parallel-controlled trial will be conducted. Three hundred eighty-four participants who meet the eligibility criteria will be randomly allocated into a control group, a CST group, a TCC group, and a combined group in a 1:1:1:1 ratio. Participants in the CST group and the TCC group will respectively receive CST and TCC training at a frequency of 1 hour per day, 5 days per week, totally 12 weeks. Participants in the combined group will receive 30 minutes CST and 30 minutes TCC training per day, 5 days per week, totally 12 weeks. No specific exercises will be required of the participants in the control group. Both musculoskeletal and cardiopulmonary function outcomes, including bone density detection, balance and coordination ability, walking ability, pain visual analogue scale (VAS) score, fall risk assessment, activities of daily living, pulmonary function tests, color sonography and electrocardiogram, will be evaluated by blinded operators at baseline, 13 weeks and 25 weeks (follow-up period).

**Discussion::**

The results of this study protocol are expected to clarify the synergistic effect of CST and TCC training on musculoskeletal and cardiopulmonary function in older adults. Furthermore, these findings will confirm whether combined or exclusive CST and TCC training, is more effective at improving functional outcomes in the elderly.

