### Sample size

2.2

We used change in bone mineral density (BMD) as the main effect indicator to estimate the sample size. Sample size calculations are performed to determine the number of participants necessary to detect effect sizes. Very few randomized controlled trials have examined the effect of TCC or CST on BMD in the elderly.

Based on similar previous studies^[19,20]^ and our preliminary experiment, the means with SDs of the BMD (lumbar spine) were X1 = 0.007 (SD1 = 0.098), X2 = 0.043 (SD2 = 0.108), X3 = 0.021 (SD3 = 0.0915), and X4 = 0.051 (SD4 = 0.099) in the CG, CST, TCC, and CTG, respectively. The sample sizes per group were calculated according to the formula: 

(i)with a type I error of 5% (α = 0.05) and 80% power (β = 0.10).(ii)K: groups, K = 4.(iii)Ψ: K = 4, V1 = K-1 = 3; V2 = N-1, N desirable maximum, Ψα, β, K-1,∞ = 2.17 (Obtained from statistical tables).(iv)X0 = (X1 + X2 + X3 + X4)/K = 0.0305.

We can calculate the number of samples as n≈80, considering a 20% dropout and exit rate. Thus, a minimum of 384 total participants is necessary to reach the target of 96 participants per group.

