### Limitations

3.1

As with most clinical studies, there are also obvious limitations in this study. Ideally, all participants in clinical randomized controlled trials should follow the blind method, but this is difficult to achieve in non-pharmacological trials.^[42]^ Although it is impossible to conduct blinding of both the coaches and participants in this trial, we will reduce the possible bias by blinding the assessors and data analysts.

In summary, the results of this trial are expected to clarify the synergistic effect of CST and TCC training on musculoskeletal and cardiopulmonary function in older adults and to confirm whether combined or exclusive CST and TCC training, is more effective at improving functional outcomes in the elderly.

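### On lumbar spine BMD, the outcome that sizes the trial, the design cannot confirm whether combined training beats CST alone: the planned difference is 0.008 with about 8% power

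*Protocol article*

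**What the plan says.** The Abstract's Discussion paragraph closes with the statement that "these findings will confirm whether combined or exclusive CST and TCC training, is more effective at improving functional outcomes in the elderly". Section 3.1 (Limitations) says the results are expected "to confirm whether combined or exclusive CST and TCC training, is more effective at improving functional outcomes in the elderly".

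The objective behind this is worded in two ways. The Abstract's Background has "The second objective is to test the effectiveness of combined physical training that incorporates CST and TCC", with no comparator. The end of the Introduction describes the same aim as testing for synergy between the two trainings.

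Section 2.2 sizes the trial on BMD and gives lumbar spine planning values for the four arms, in the order control, CST, TCC and combined: "X1 = 0.007 (SD1 = 0.098"), "X2 = 0.043 (SD2 = 0.108"), "X3 = 0.021 (SD3 = 0.0915") and "X4 = 0.051 (SD4 = 0.099) in the CG, CST, TCC, and CTG, respectively". It arrives at about 80 per group, raised to 96 per group (384 in total) for 20% dropout.

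Section 2.13 plans an overall ANOVA or Kruskal–Wallis test at two-sided 5%, with a Bonferroni adjustment for multiple outcomes. It analyses by intention to treat, with last observation carried forward, and per protocol.

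**The concern.** Saying which of combined or single training is more effective takes two comparisons: combined minus CST and combined minus TCC. The overall four-group test does not supply them. It can be significant only because the control arm lies below the rest.

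The planning means place combined training and CST almost together. If the trial behaves as its designers assume, the comparison that limits this conclusion will almost always be non-significant on BMD, with an interval that allows a clear advantage in either direction. A trial announced as confirming the answer then has no answer to give on the outcome that fixed its size. What is at stake is the conclusion the report may draw about combined versus single training.

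**Working it through.** **Inputs (section 2.2; section 2.13 for the test level).** Means (SD): control 0.007 (0.098), CST 0.043 (0.108), TCC 0.021 (0.0915), combined 0.051 (0.099). Randomised per arm: 96. After 20% dropout: 96 × 0.8 = 76.8, about 77. Two-sided α = 0.05, unadjusted.

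**The plan's own figures.** The grand mean reproduces: (0.007 + 0.043 + 0.021 + 0.051)/4 = 0.0305. So does the step to 96: 80 × 1.2 = 96. The figure of about 80 does not reproduce under the usual four-mean formula, n = Ψ² × (mean of the SD²) / [Σ(Xi − X0)²/3]. With Ψ = 2.17 this gives about 114. The printed formula is missing from the text available, so its form is an assumption here. That is a separate matter: the steps below use only the means, the SDs and the planned arm size.

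**Combined minus CST.**
- Difference: 0.051 − 0.043 = 0.008.
- SE = √[(0.099² + 0.108²)/76.8] = √(0.021465/76.8) = 0.0167.
- 95% CI half-width: about 1.98 × 0.0167 = 0.033, four times the difference.
- Difference/SE = 0.48. Power ≈ Φ(0.48 − 1.96) + Φ(−0.48 − 1.96) ≈ 0.07 + 0.01, about 8%. The noncentral t calculation gives 7.6%.
- Per-arm size for 80% power: (0.099² + 0.108²) × (1.96 + 0.84)² / 0.008² ≈ 2,630.
- Difference that would have 80% power at the planned size: 2.80 × 0.0167 = 0.047. This exceeds the whole assumed effect of combined training over control, 0.051 − 0.007 = 0.044.

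**Combined minus TCC.**
- Difference: 0.051 − 0.021 = 0.030.
- SE = √[(0.099² + 0.0915²)/76.8] = 0.0154.
- Difference/SE = 1.95; power about 49%.

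**Sensitivity to the number analysed (noncentral t, unadjusted).**

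| Comparison | Difference | 77 per arm | 80 per arm | 96 per arm |
|---|---|---|---|---|
| Combined vs CST | 0.008 | 7.6% | 7.7% | 8.3% |
| Combined vs TCC | 0.030 | 49% | 51% | 58% |
| Combined vs control | 0.044 | 79% | 80% | 87% |

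Combined versus control is shown for scale only. Its 79% falls once the plan's Bonferroni adjustment applies, for example to 69% at α = 0.025. Adjustment lowers the other two rows as well.

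**Sensitivity to the SD.** For 0.008 to have 80% power at 76.8 per arm, the SD would have to be 0.008 / (2.80 × √(2/76.8)) = 0.008/0.452 ≈ 0.018. The pair's root-mean-square SD is √(0.021465/2) = 0.1036, nearly six times as large.

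**The case against.** **The promise is wider than BMD.** It speaks of functional outcomes. Section 2.12 also makes cardiopulmonary function primary and lists balance, flexibility, fall risk and daily living as secondary. This stands in part. The Abstract's Methods counts bone density among the function outcomes, and BMD is the only one with planning values, but a reader who infers that the promise as a whole has 8% power goes too far. Nothing in the document allows power to be computed for the rest.

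**Naming contrasts is commonly left to the analysis plan.** This also stands, and the absence of named pairwise tests is not the point. The point is a conclusion that the article states and its own means do not support. An analysis plan cannot change that.

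**The wording is aspirational.** Section 3.1 does speak only of expectation. The Abstract does not; it says the findings will confirm.

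**Stronger readings that the documents do not support.** A reader might infer that the second objective really means combined versus control, and that this should become the confirmatory test because it has about 79% power. The Background names no comparator, the Introduction frames the aim as synergy, and a control comparison alone answers neither synergy nor the question of combined or single. The 79% is also unadjusted. A reader might further infer that the arms will be ranked by their observed means, or that non-significance will be read as equality. The document plans neither.

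**Conclusion.** The concern holds, limited to lumbar spine BMD and to the claim that the trial will confirm which of combined or single training is more effective. Under the plan's own means and SDs, combined versus CST has about 8% power at any arm size from 77 to 96, before adjustment. The interval would be about ±0.033 around an expected difference of 0.008. Combined versus TCC is close to an even chance (49% at 77 per arm). The trial cannot confirm combined versus CST on the outcome that sizes it.

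This rests on the section 2.2 planning values, a two-sample comparison at two-sided 5%, and 20% dropout. The result for combined versus CST does not depend on the dropout assumption, and it would change only if the true difference were several times larger or the SD several times smaller than planned. Nothing is concluded about the other outcomes.

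**What to change.** 1. In the Abstract's Discussion and in section 3.1, withdraw the verb confirm for combined versus single training. Say instead that the trial will estimate, with 95% confidence intervals, the difference between combined training and each single training.
2. In section 2.13, add those two estimates (combined minus CST and combined minus TCC) alongside the overall ANOVA.
3. State there that a non-significant difference will not be read as equal effectiveness.

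This needs no extra participants or measurements. The cost is a less ambitious claim on a question the authors present as new. Changing the second objective to combined versus control is not part of the fix. If that comparison is mentioned, give its power as about 79% unadjusted at 77 per arm, about 87% if all 96 are analysed, and lower after the Bonferroni adjustment.

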**Trial registration::**

Chinese Clinical Trial Registry: ChiCTR-IOR-17010769. Registration date: March 3, 2017.

## Introduction

1

According to the sixth national census report in China, 13.26% of the total population are 60 years of age or older and 8.87% of the total populations are 65 years of age or older.^[1]^ These numbers suggest that China is facing the challenges of an aging population, and aging has become an irreversible worldwide trend in the twenty-first century. Advancing age is related to considerable changes in mental and physical health, including a loss of muscle mass and weakened musculoskeletal function.^[2]^ Furthermore, The elderly are at a risk of weakening respiratory function, given the age-related decline in lung function and respiratory muscle strength, as well as the age-related onset and progression of cardiopulmonary disease.^[3]^ All these factors associated with aging can lead to impaired physical function and mobility and reduce quality of life (QOL).^[4]^

More and more studies have proved that regular exercise or physical activities are good for physical and psychological health outcomes.^[5,6]^

Moreover, physical activity can enhance the functioning of cardiovascular systems and reduce cardiovascular risk.^[7,8]^ Tai Chi Chuan (TCC) has been practiced in China, Japan, South Korea, and other Asian countries for hundreds of years, especially in the elderly. TCC is a traditional physical and mental training that is light to medium intensity, depending on training style, posture, and duration. A large number of previous studies have shown that TCC can improve the body's aerobic capacity, muscle efficacy,^[9]^ and psychological well-being. In addition, TCC is beneficial to reduce common cardiovascular risk factors, such as hypertension, diabetes, dyslipidemia, and depression.^[10,11]^

Strength training has recently become a hot topic in many clinical studies, including the elderly.^[12,13]^ There are many studies indicating that strength training can improve the mobility of the human body (e.g., increase gait speed and distance), functional tasks (e.g., standing and shifting), and basic daily life functions of the elderly.^[14,15]^ In many sports activities, people have been increasingly aware of the importance of the central core of the body for stabilization and power generation. “Core stability’” refers to the ability to control the position and movement of the trunk over the pelvis so as to make the best production, transfer, and control of force and motion to the terminal segment during the comprehensive movement. Rehabilitation should include the restoration of the core itself and the core as the base for extremity function.^[16,17]^ In a recent study, the researchers conducted a nine-week progressive core strength training (CST) study on the unstable surface among the elderly in the community. It was concluded that CST conducted on unstable surfaces is a feasible and effective exercise programme to alleviate age-related performance decline.^[18]^

As mentioned above, both methods of physical training have positive effects on the outcome of human health. However, it is difficult to draw firm conclusions because limitations or biases exist in most studies due to factors such as insufficient sample size or a lack of strict randomized design. In addition, there is no systematic comparison of the effects of TCC and CST, nor has the possibility of a synergistic effect of the two physical training combinations been evaluated. The aims of this study protocol are to evaluate the effects of CST compared to those of TCC on the outcomes of the musculoskeletal system and cardiopulmonary function in older adults and to test the synergistic effect of a combined physical training of CST and TCC.

## Materials and methods

2

### Study design and setting

2.1

This study is a randomized, single-blind, parallel-controlled trial. Participants will be randomly allocated into 4 groups:(i)control group (CG): routine activities of daily living;(ii)CST group: routine activities of daily living plus core strength training;(iii)TCC group: routine activities of daily living plus TCC; and(iv)combined training group (CTG): routine activities of daily living plus core strength training and Tai Chi Chuan.

All participants will receive the same intervention time of 1 hour/day, 5 days/week for a total of 12 weeks. Both musculoskeletal and cardiopulmonary function outcomes, including bone density detection, balance and co-ordination ability, walking ability, pain visual analogue scale (VAS) score, fall risk assessment, activities of daily living, pulmonary function test, color sonography, and electrocardiogram will be evaluated by the blinded assessors at the People's Hospital of Ningxia Hui Autonomous Region at baseline, at 13 weeks (end of the intervention), and at 25 weeks (12 weeks after follow up). At the end of each month during the intervention period, there will be professional trainers to guide the participants to ensure that the participants are trained correctly. The flow diagram of the entire trial programme is illustrated in Figure 1.

**Figure 1 F1:**
[figure not shown]
Flow diagram of participants.

### Sample size

2.2

We used change in bone mineral density (BMD) as the main effect indicator to estimate the sample size. Sample size calculations are performed to determine the number of participants necessary to detect effect sizes. Very few randomized controlled trials have examined the effect of TCC or CST on BMD in the elderly.

Based on similar previous studies^[19,20]^ and our preliminary experiment, the means with SDs of the BMD (lumbar spine) were X1 = 0.007 (SD1 = 0.098), X2 = 0.043 (SD2 = 0.108), X3 = 0.021 (SD3 = 0.0915), and X4 = 0.051 (SD4 = 0.099) in the CG, CST, TCC, and CTG, respectively. The sample sizes per group were calculated according to the formula: 

(i)with a type I error of 5% (α = 0.05) and 80% power (β = 0.10).(ii)K: groups, K = 4.(iii)Ψ: K = 4, V1 = K-1 = 3; V2 = N-1, N desirable maximum, Ψα, β, K-1,∞ = 2.17 (Obtained from statistical tables).(iv)X0 = (X1 + X2 + X3 + X4)/K = 0.0305.

We can calculate the number of samples as n≈80, considering a 20% dropout and exit rate. Thus, a minimum of 384 total participants is necessary to reach the target of 96 participants per group.

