### Statistical analysis

2.13

We will use the intention-to-treat (ITT) analysis and per-protocol subject (PPS) analysis to analyze the primary and secondary outcomes. When there is a missing data, we will use the last observation carried forward method to deal with it. The continuous variables will be expressed as the mean ± SD. All categorical variables will be expressed in terms of their standard error. After examining whether the data accord with normality test (the Kolmogorov–Smirnov test), we will use ANOVA (assuming a normal distribution) or Kruskal–Wallis (a nonparametric test) to analyze the measurement results. We will use the Bonferroni method to appropriately adjust the overall level of significance for multiple outcomes.

For all the analyses of this study a significance level of 95% (two-sided *P* < .05) will be used. All statistical tests will be conducted using SPSS Statistical Software (IBM SPSS Statistics for Windows, Version 21.0. Armonk, NY).

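### The sample size of 80 per group does not follow from the plan's own inputs, its power and β contradict each other, and 384 participants with 20% loss give about 73% power

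*Protocol article*

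**What the plan says.** Section 2.2 (Sample size) of the Protocol article names the sizing variable: "We used change in bone mineral density (BMD) as the main effect indicator to estimate the sample size". The error rates are given as "with a type I error of 5% (α = 0.05) and 80% power (β = 0.10").

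The assumed means and SDs for lumbar spine BMD are, for control and core strength training, "X1 = 0.007 (SD1 = 0.098), X2 = 0.043 (SD2 = 0.108"), and for Tai Chi Chuan and combined training, "X3 = 0.021 (SD3 = 0.0915), and X4 = 0.051 (SD4 = 0.099"). The section gives K = 4, a grand mean of 0.0305, and "Ψα, β, K-1,∞ = 2.17 (Obtained from statistical tables").

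The result is "We can calculate the number of samples as n≈80, considering a 20% dropout and exit rate", followed by "Thus, a minimum of 384 total participants is necessary to reach the target of 96 participants per group". Section 2.13 (Statistical analysis) plans ANOVA, or Kruskal–Wallis if normality fails, at a two-sided 5% level.

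**The concern.** Three things in one short paragraph do not fit together.

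- The power and the β describe different targets: 80% power is β = 0.20, and β = 0.10 is 90% power.
- The listed inputs do not appear to give 80 per group under either target.
- The step from 80 to 96 is 80 × 1.2. Multiplying by 1.2 does not preserve 80 after a 20% loss.

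This is the only sample size justification in the article, and BMD is a primary outcome (section 2.12.1). If the true power is well below the stated figure, a null BMD result would be read as stronger evidence of no effect than it is. The Introduction also faults earlier studies for being too small.

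**Working it through.** **Inputs (section 2.2).** Means 0.007, 0.043, 0.021, 0.051; SDs 0.098, 0.108, 0.0915, 0.099; K = 4; α = 0.05; Ψ = 2.17; 20% loss; 96 per group.

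**Step 1: the plan's grand mean.** (0.007 + 0.043 + 0.021 + 0.051)/4 = 0.0305. This reproduces.

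**Step 2: spread and variance.**
- Deviations from 0.0305: −0.0235, 0.0125, −0.0095, 0.0205.
- Sum of squares: 0.000552 + 0.000156 + 0.000090 + 0.000420 = 0.001219.
- Mean variance: (0.009604 + 0.011664 + 0.008372 + 0.009801)/4 = 0.009860, a common SD of 0.0993.

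**Step 3: which power does Ψ = 2.17 belong to?** With 3 and ∞ degrees of freedom, Ψ = √(λ/3), where λ is the noncentrality of a 3-df chi-square test at α = 0.05.
- 90% power: λ = 14.17, Ψ = 2.173.
- 80% power: λ = 10.90, Ψ = 1.906.

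So 2.17 matches β = 0.10, not the stated 80% power.

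**Step 4: n per group.** The formula is not in the text available. The listed arguments (Ψ, K, grand mean, SDs) point to n = Ψ² × (ΣSDᵢ²/K) / [Σ(Xᵢ − X₀)²/(K − 1)]. The denominator is 0.001219/3 = 0.0004063.
- Ψ = 2.17: 4.709 × 0.009860/0.0004063 = 114.3.
- Ψ = 1.906: 88.2.
- Ψ needed to obtain exactly 80: 1.816, which is neither tabled value.

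Variants do not give 80 either. With Ψ = 2.17, dividing by K instead of K − 1 gives 152, the smallest and largest SD give 97 and 135, and leaving Ψ unsquared gives 53. With Ψ = 1.91, the smallest and largest SD give 75 and 105.

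**Step 5: dropout.** 80 × 1.2 = 96. A 20% loss leaves 96 × 0.8 = 76.8. To keep 80 evaluable, 80/0.8 = 100 must be randomised.

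**Step 6: power of the planned ANOVA.** Noncentral F with 3 and 4(n − 1) degrees of freedom and λ = n × 0.001219/0.009860. This step does not use the inferred formula.

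| Evaluable per group | λ | Power |
|---|---|---|
| 76.8 (96 less 20%) | 9.49 | 73.1% |
| 77 | 9.52 | 73.2% |
| 80 | 9.89 | 75.0% |
| 90 | 11.13 | 80.4% |
| 96 (no loss) | 11.87 | 83.2% |
| 116 | 14.34 | 90.1% |

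**Step 7: what each target requires.**
- 80% power: 90 evaluable; 90/0.8 = 112.5, so 113 randomised per group, 452 in total.
- 90% power: 116 evaluable; 116/0.8 = 145 per group, 580 in total.
- At 96 per group, 80% power holds only while at least 90 are evaluable, that is, a loss of at most 6/96 ≈ 6%.

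**The case against.** **The formula is not visible, so 114 and 88 rest on a reconstruction.** True, but the listed arguments identify it well, and the power figures in step 6 do not use it. At 80 per group the planned F test has 75% power whatever formula was printed.

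**A pairwise calculation comes close to 80.** Control against combined training at 80% power needs 79 per group. The section describes a four-group calculation with K = 4 and Ψ, so this does not explain the stated number.

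**The 73% is one scenario.** It counts completers only, at the full 20% loss, with equal variances. Section 2.13 plans an intention-to-treat analysis with last observation carried forward, and section 2.14 seeks a final assessment before withdrawal, so all 96 might be analysed. This is the strongest point, but it does not restore the claim. A participant with no measurement after baseline contributes a change of zero. If 20% of each group do so, the means shrink to 0.8 of their values, the sum of squares becomes 0.64 × 0.001219 = 0.000780, the mean variance becomes 0.008086, and λ = 96 × 0.000780/0.008086 = 9.26, about 72% power. Real final measurements from some leavers would move power towards 83%, which is reached only with none missing.

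**The inflation error is small.** It stands that its own effect is minor: 75.0% falls to 73.1%. The main defect is that β, Ψ and n do not agree.

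**Against 80%, the shortfall is only about 7 points.** Correct, and with high retention 96 per group exceeds the 90 needed. Against the 90% that β and Ψ imply, even full retention falls short.

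**Conclusion.** The concern holds. The stated power and β contradict each other, Ψ = 2.17 belongs to 90% power, and 80 per group follows from neither target: the inputs give about 114 (exact F test 116) for 90% and about 88 (exact 90) for 80%. Inflation by 1.2 adds a smaller error.

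At the plan's own 20% loss, 384 participants give about 73% power for the BMD comparison, a type II risk of about 27%. With no loss, power is 83%. These figures take the plan's means and SDs as given, assume equal variances and an omnibus ANOVA at α = 0.05, and treat 80 as the number before dropout. If 80 already allowed for dropout, 64 per group would be evaluable and power at that number would be 64%.

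The text must be corrected because it states a power that the design does not deliver under its own assumptions.

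**What to change.** Revise section 2.2 as follows:

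1. State one target: either 80% power with β = 0.20 and Ψ ≈ 1.91, or 90% power with β = 0.10 and Ψ = 2.17.
2. Give the n per group that the inputs yield: about 88–90 for 80%, or about 114–116 for 90%.
3. Replace multiplication by 1.2 with division by (1 − 0.20).
4. If 384 is kept, say that it was fixed at that number and report the power it delivers: about 73% at 20% loss and 83% with no loss, with 80% reached only if loss is about 6% or less.

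This costs a rewording of one section and a less favourable power statement. Recruitment, randomisation and analysis do not change. If the sponsor wants 80% power at 20% loss, the price is 452 − 384 = 68 more participants; 90% would need 580 − 384 = 196 more.
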